### 3. STUDY DESIGN

The study design is illustrated in Figure 1 (next page). Patients participate after Informed Consent is obtained. In the dark blue squares of the figure, the different subsequent steps after inclusion are noted. The different time-points for follow-up are outlined in the yellow squares.

When subjects are selected, the following characteristics will be documented in a Case Report Form: gender, age, highest level of education, duration of unilateral deafness, anatomical and aetiological issues as well as psychological and motivational attributes.

After inclusion, subjects will be randomly allocated (see section 6.2 Randomisation, blinding and treatment allocation) to one of three treatment groups:

1. Group A: cochlear implantation
2. Group B: 6-week during test periods with first BAHA, then CROSS
3. Group C: 6-week during test periods with first CROSS, then BAHA

Subjects in group A, the cochlear implantation group, will receive a CI directly after randomisation. The device will be programmed 3-7 weeks after surgery, which is standard CI care.

Subjects in group B shall start with a 6 weeks during test period with a BAHA on a headband. After the 6 weeks, these subjects switch to another test period of 6 weeks with a CROSS. In group C, subjects start with a CROSS and after their first 6-week test period they switch to a test period with a BAHA on headband for 6 weeks. After these two test periods, three questionnaires will be filled out (SSQ, APHAB and GBI; see Section 6.1.2. Secondary study parameters/endpoints). The participants in groups B and C complete both test periods after 12 weeks. The reason for this cross-over is to control for bias caused by the order effect, which means that participants will judge the second modality influenced by their experience using the first modality. Since we have created two groups with the opposite sequence, the order effect is eliminated. After completing both test periods, subjects will be seen in our clinic and have to choose for further treatment with either CROSS, a definitive surgically implanted BAHA or no treatment (if they found none of the modalities helpful).

Figure 1: study design

[figure not shown]

Legend: SSD: single-sided deafness, N: number of subjects, CI: cochlear implant; BAHA\*: bone-anchored hearing aid on headband, BAHA (def): definitive surgically implanted BAHA, CROSS: contralateral routing of sound system, FU: follow-up.

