In all groups the objective and subjective follow-up measurements shall take place at the same time-points. All questionnaires outlined in section 6.1.2. will be filled out.

During the first two years, subjects will be evaluated at 6, 12, 18 and 24 months after randomisation. During this period, the cost utility diary will be filled out every month. Afterwards, we will continue with follow-up on yearly basis for 3 more years (i.e. 36, 48 and 60 months post-randomisation). The cost utility diary will then be filled out every 3 months, to minimize subject burden.

A sample size of 30 subjects in group A and 45 subjects in group B and C each is designed to allow valid statistical assessment of cochlear implant benefit (see Section 4.4 Sample size calculation).

Patients with an onset of unilateral hearing loss between  $\geq 3$  months and  $\leq 10$  years before time of inclusion are eligible for inclusion (see also Section 4.2 Inclusion criteria). The reason for the three month interval after onset of deafness is that clinical practice nowadays is to first treat without hearing aids (for instance for sudden deafness with corticosteroids) and to await the natural course of the deafness. When the patient remains unilaterally deaf, he/she is eligible for inclusion in the study. When patients became deaf before this study was started, they are eligible for this study when the duration of deafness is  $\leq 10$  years. During this interval, adaptation to the monaural situation occurs and becomes irreversible thereafter. That is the reason why this cut-off point is established.

Subjects shall be randomised into one of the three groups using a strict randomisation process (see Section 6.2 Randomisation, blinding and treatment allocation). Subjects willing to participate must be informed that they can be assigned to either modality and accept to submit to this randomisation. It is only after the subject has signed their consent form that he/she is informed of the assigned group.

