## **4.2 Inclusion criteria**

- Patients aged 18 or older.
- Acute onset of postlingual SSD, defined as onset unilateral hearing loss between  $\geq 3$  months and  $\leq 10$  years before time of inclusion.
- Hearing measurements:
  - Pure Tone Audiometry of the deaf ear, defined as thresholds of 70 dB or higher on frequencies 0,5 – 4.0 kHz (average).
  - Normal hearing on the contralateral ear, defined as pure tone audiometry thresholds of 30 dB or less on frequencies 0.5 – 4.0 kHz (average).
  - Air bone gap  $\leq 10$  dB.
- Normal function of middle ear (i.e. no acute middle ear infections or tympanic membrane perforations).
- Dutch language proficiency.
- Willingness and ability to participate in all scheduled procedures outlined in the protocol.
- General health allowing general anaesthesia for the potential surgical implantation of a CI or BAHA.
- Patients covered by the Dutch health insurance.
- Patients should agree to be implanted with a CI or BAHA.
- Informed consent understood, filled out and signed by patient.
- Patients are not allowed to participate in another ongoing research study related to SSD or cochlear implantation.

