## **4.4 Sample size calculation**

To detect a clinically relevant difference of 5 dB SNR (standard deviation 5 dB) between the groups on the modified Plomp test, with an alpha of 0.05 and a power of 95%, 27 subjects

per group are needed. To be safe, a 10% margin is used to compensate for potential dropouts (e.g. non user cochlear implantees), resulting in 30 patients in the CI group. From recent literature we know that 55% of BAHA-on-headband users are not satisfied after their trial period and choose not to be implanted with a BAHA (Desmet 2012). Therefore, we must include more patients in groups B and C for compensation of the patients ending up in the 'no treatment' group. According to this proportion, 40 patients will end up with a BAHA. Patients not opting for a BAHA can choose for a CROSS. Based on many years of experience at our Audiologic Center, we expect ~60% to choose for CROSS. Thus, predicted numbers per group will be: CI (30), implanted BAHA (40), CROSS (30), 'no treatment' (20), leading to  $n = 45$  for groups B and C. These numbers allow for a valid calculation of the clinically relevant difference on the modified Plomp test.

Based on figures from the UMC Utrecht (in Dutch: Bedrijfsbureau DHS), approximately 25-30 patients per year with SSD present at the ENT outpatient department. Together with patients from the peripheral area of the UMC Utrecht, we expect the inclusion of patients to last for 3-4 years after the inclusion of the first patient. We also expect single-sided deaf patients from other areas of the country to present at the ENT department at the UMC Utrecht.

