### 6.2 Randomisation, blinding and treatment allocation

120 subjects will randomly be assigned to one of the three study groups: 30 in the CI group, 45 in the first-BAHA group and 45 in the first-CROSS group. A website randomisation

program, developed by the Julius Center, UMC Utrecht (<http://www.juliuscentrum.nl/random/>) shall be used to divide the subjects into the groups.

The randomisation chart is established before the start of the study by an independent data manager. When a local executor recruits a subject, the physician can log on to the site and enter the subject's characteristics. A block randomisation model will be used to make sure that the ratio CI:CROSS:BAHA subjects will be about equal ( $30:45:45 = 2:3:3$  per block). The physician will receive an allocation group number on his/her screen within a few seconds. It is only after the subject has signed the Informed Consent form that he/she is randomised and informed of the assigned group.

Logically, blinding is not possible since both patients and doctors will be able to see from the outside whether subjects have received a CI, BAHA or CROSS.

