## **8. STATISTICAL ANALYSIS**

The aim of the study is to evaluate the clinical outcome after cochlear implantation, compared to BAHA, CROSS or unaided conditions, measured as speech perception in noise, sound localization, tinnitus and quality of life in patients with SSD. Also, a cost utility analysis will be performed (see section 6.3.2).

Overall, the study is an RCT, but subjects in group B and C run through the same two test periods within the first 3 months, afterwards they shall be treated with their modality of choice. As discussed previously, we expect 55% of patients in group B and C to choose for no treatment, we randomise more subjects in these groups (Desmet 2012). Thus equal comparison with the CI group will be possible during follow-up.

Major test intervals are the same in all study groups, namely 6, 12, 18, and 24 months after randomisation. After the first two years, subjects will be evaluated on yearly basis for three more years (36, 48 and 60 months).

The primary outcome will be the performance on the modified Plomp hearing test. The data are quantitative and will be presented as continuous variables. Between-group mean differences, rate differences and rate ratios with 96% confidence intervals will be calculated. Differences between the three groups will be analysed using the Kruskal Wallis test.

The secondary outcomes will be the performances on the other auditory tests and the questionnaires (see Section 6.3). Analyses of between-group differences will be performed with Chi-square-tests for categorical outcomes and Kruskal Wallis tests for continuous outcomes. Within-subject comparisons will entail differences of mean values. These will be analysed using paired t-tests for continuous measures.

Missing values will be imputed using multiple imputation and all analyses will be performed on an intention-to-treat basis.

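### Section 8 fixes an unadjusted Kruskal-Wallis test for the primary SRT although better-ear thresholds, age and duration of deafness are recorded before treatment; a prespecified covariate-adjusted estimate would cost almost nothing and could sharpen differences below 5 dB

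*Protocol*

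**What the plan says.** Protocol section 8 names the primary test: "Differences between the three groups will be analysed using the Kruskal Wallis test". The same paragraph promises between-group mean differences with confidence intervals but does not say which model produces them. No covariate or adjusted analysis appears anywhere in the protocol.

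Three variables that could serve as covariates are available before treatment:

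- **Age and duration of deafness.** Section 3 lists, for the case report form at selection, "gender, age, highest level of education, duration of unilateral deafness, anatomical and aetiological issues".
- **Better-ear thresholds.** Section 5.1 puts pure tone audiometry on the baseline list. Section 4.2 needs the better-ear average for eligibility: "Normal hearing on the contralateral ear, defined as pure tone audiometry thresholds of 30 dB or less on frequencies" from 0.5 to 4.0 kHz.

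The modified Plomp test itself is not on the baseline list in section 5.1.

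On duration, section 3 explains the 10-year limit thus: "During this interval, adaptation to the monaural situation occurs and becomes irreversible thereafter".

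On allocation, section 6.2 says: "A block randomisation model will be used to make sure that the ratio CI:CROSS:BAHA subjects will be about equal", in the ratio 2:3:3. No stratification factor is named. The physician enters subject characteristics on the randomisation site, but their use is not stated.

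**The concern.** The primary score is taken in the best aided condition, with speech and noise both from the front (sections 6.1.1 and 6.3.1). The hearing ear therefore contributes in every arm, and its average threshold may lie anywhere up to 30 dB. By the protocol's own reasoning, duration of deafness matters to what can be regained. If these variables predict the SRT, part of the 5 dB standard deviation is variation that the trial has already measured, and the named test cannot remove it.

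At stake are the width of the interval around the CI effect and the power for differences smaller than the planned one. Such differences are not remote. The primary set-up does not separate speech from noise, and section 1.2 puts the benefit of binaural summation at 2 to 6 dB. With only 30 patients in the CI arm, a chance imbalance in a prognostic variable would also pass into the unadjusted estimate.

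**Working it through.** **Inputs.** Section 4.4 gives the target: "To detect a clinically relevant difference of 5 dB SNR (standard deviation 5 dB) between the groups on the modified Plomp test". It sets the type I error at 0.05 and the power at 95%, arrives at 27 in each group, and raises the CI arm to 30 as a 10% allowance for drop-out. Section 6.2 gives the allocation, 30:45:45. R2, the share of SRT variance explained by the covariates, is not in the protocol. It is assumed here, over the range 0 to 0.5.

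**1. The plan's own figure.** An exact two-sided two-sample t-test for 5 dB with SD 5 dB, alpha 0.05 and power 95% needs 26.99, so 27 per group (the normal approximation gives 26). With the 10% margin, 27/0.9 = 30. The stated figures reproduce, and they use an unadjusted SD.

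**2. Standard error with and without adjustment.** Residual SD = 5 × √(1 − R2). SE = SD × √(1/nA + 1/nB).

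| R2 (assumed) | Residual SD (dB) | SE, 30 v 45 (dB) | SE, 30 v 90 (dB) |
|---|---|---|---|
| 0 | 5.00 | 1.18 | 1.05 |
| 0.1 | 4.74 | 1.12 | 1.00 |
| 0.3 | 4.18 | 0.99 | 0.88 |
| 0.5 | 3.54 | 0.83 | 0.75 |

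The unadjusted SE exceeds the adjusted one by the factor 1/√(1 − R2): about 5% at R2 = 0.1, 20% at 0.3 and 41% at 0.5.

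**3. Power of the planned test.** Simulation with 4,000 runs per setting, three randomised groups of 30, 45 and 45, one normal covariate, normal errors, a shift in the CI arm only and no drop-out. Kruskal-Wallis is set against analysis of covariance (ANCOVA):

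| R2 (assumed) | True 0 dB: K-W / ANCOVA | True 3 dB: K-W / ANCOVA | True 5 dB: K-W / ANCOVA |
|---|---|---|---|
| 0 | 0.052 / 0.055 | 0.69 / 0.71 | 0.99 / 0.99 |
| 0.1 | 0.047 / 0.052 | 0.68 / 0.76 | 0.99 / 1.00 |
| 0.3 | 0.047 / 0.043 | 0.69 / 0.87 | 0.99 / 1.00 |
| 0.5 | 0.053 / 0.053 | 0.67 / 0.96 | 0.99 / 1.00 |

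The 0.69 against 0.71 at R2 = 0 does not come from the covariate, which explains nothing there. With normal errors, a linear-model test is slightly more powerful than a rank test.

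**4. Chance imbalance.** For a standardised covariate, the SD of the difference in means is √(1/nA + 1/nB): 0.236 for 30 v 45 and 0.211 for 30 v 90. The probability of a gap above 0.3 SD is then about 0.20 and 0.16, and above 0.5 SD about 0.03 and 0.02. A gap of 0.3 SD shifts the unadjusted difference by 0.3 × √R2 × 5 dB: 0.47 dB at R2 = 0.1, 0.82 dB at 0.3 and 1.06 dB at 0.5.

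**The case against.** The strongest reply is that nothing here is invalid. An unadjusted test in a randomised trial holds its error rate (0.047 to 0.053 in the simulation), chance imbalance is already covered by that error rate and by the interval, and at the planned 5 dB there is nothing left to gain. All of this stands. A reader might infer that the primary result would be biased or the trial underpowered for its target; the figures do not support either.

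It can also be said that the protocol never shows these variables to predict the score. That stands too:

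- **Better ear.** Section 6.3.1 tests each patient at the level of their own best word score in quiet, and eligibility caps the average at 30 dB. Both may weaken the link.
- **Age.** The protocol says nothing about it as a predictor.
- **Duration.** Section 3 argues for the 10-year cut-off. It does not say that duration within the window determines the response to a CI. If duration acted only in the CI arm, a main-effect covariate would correct an imbalance only in part.

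A reader might further infer that the list is certainly unstratified. Section 6.2 names no stratum but leaves the use of the entered characteristics open, so this is a matter to clarify.

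Two replies carry less weight. One is that adjustment belongs to an unseen SAP; but section 8 itself fixes the primary test. The other is that a rank test is safer, since section 6.3.1 notes that some CI users cannot repeat whole sentences even in quiet. That is a reason to keep the rank test as a check. It weighs less against a linear model here, because the score is taken in the best aided condition with a near-normal ear and section 8 already promises mean differences, which Kruskal-Wallis does not give.

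**Conclusion.** The point holds as a matter of efficiency. Section 8 commits the primary outcome to a test that cannot use three pre-treatment variables already collected and plausibly prognostic.

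The size is conditional on R2. At 10% to 30%, power at a true 3 dB rises by roughly 8 to 18 percentage points, of which about 2 points reflect the change from ranks to a linear model under normal errors. A 0.3 SD imbalance, with a probability of about 0.16 to 0.20 for any one covariate, would move the unadjusted CI estimate by about 0.5 to 0.8 dB. At R2 = 0 the covariates gain nothing.

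These figures assume a linear covariate effect common to all arms, normal errors and comparison of the groups as randomised. The statement that precision is lost cannot be made outright, because the protocol gives no R2.

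**What to change.** In section 8, specify that the between-group mean differences and their intervals for the modified Plomp SRT come from a linear model with randomised group, better-ear pure tone average, age and duration of deafness, all taken before treatment. Make this the primary estimate. Keep Kruskal-Wallis as a sensitivity analysis in case the SRT distribution is irregular. Settle the covariates and their form before outcome data are examined.

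In section 6.2, state what the subject characteristics entered on the randomisation site are used for. Stratifying by duration of deafness, with one cut-off fixed beforehand, is optional and possible only if recruitment has not started. The adjusted analysis does not depend on it.

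The cost is wording only: no new measurement and no extra patients. The small downside is reliance on a linear model and three degrees of freedom (with 120 patients and three groups, 114 residual instead of 117).

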## 5. TREATMENT OF SUBJECTS

### ***5.1 Investigational product/treatment***

Before study inclusion, subjects will receive standard workup for the diagnosis SSD. This ENT workup includes a clinical history and interview, otologic examination, audiological testing and a MRI-scan for auditory nerve evaluation. Additionally, to determine eligibility for cochlear implantation, a CT-scan will be made to visualize the anatomy of the mastoid. When the diagnosis SSD is sure, all inclusion criteria are met and anatomy permits cochlear implantation, inclusion and randomisation will take place.

Subjects will be asked to read and sign the Informed Consent form presented by the patient's ENT-surgeon before randomisation. This physician will fill in a Demographics Form to gather subject information.

Baseline evaluation for gathering study related data will take place locally at randomisation:

- Pure tone audiometry
- Speech audiometry (CVC [consonant-vowel-consonant] score in quiet)
- Questionnaires: SSQ, HUI3, GBI, APHAB, TTO, VAS, EQ5D, HADS, and Tinnitus questionnaires.

The patients will be asked to fill in a monthly costs diary starting on the first day after inclusion until the end of the second year of the study. From then on, they will complete the costs diary once per 3 months.

For all patients in group A (CI group) and those in group B or C preferring BAHA implantation preoperative medical evaluation will be carried out locally by the anaesthesiologist and includes a determination of general health status and suitability for surgery. Subjects in the CI group will also be evaluated by the center's Cochlear Implant Team, as is standard care for cochlear implantees. The standard surgical procedures developed for placement of the BAHA and the internal components of the CI will be followed. Specific procedures for implanting of the devices will be left to the discretion of the surgeon.

The first evaluation visit will occur approximately 3 to 7 weeks after surgery in the CI group to custom fit the processor software. It will be programmed for optimal speech perception, based on individual subject preferences.

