#### Tinnitus Questionnaires

- The *Tinnitus Handicap Inventory (THI)* has 3 subscales: a functional subscale (11 items), an emotional subscale (9 items) and a catastrophic subscale (5 items).

- *The Tinnitus Questionnaire (TQ)* encompasses 52 questions on tinnitus related to: emotional distress, cognitive distress, intrusiveness, auditory perceptual difficulties, sleep disturbance and somatic complaints.
- *The Tinnitus Burden Questionnaire*: This questionnaire contains 12 questions on the severity and character of tinnitus described by subjects.

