## **7.2 Adverse and serious adverse events**

Adverse events (AEs) are defined as any undesirable experience occurring to a subject during a clinical trial, whether or not considered related to the investigational drug or intervention. All adverse events reported spontaneously by the subject or observed by the investigator or his staff will be recorded.

Besides the normal risks associated with surgery and general anaesthesia, AEs related to cochlear implantation or BAHA could be: implant failure, irritation, pain or infection and implant extrusion. Some specific AEs for cochlear implantation are complaints associated with electrical stimulation (i.e. tinnitus, facial nerve stimulation, dizziness) or uncomfortably loud sound sensation or no sound sensation due to failure of component parts.

A serious adverse event (SAE) is any untoward medical occurrence or effect that at any dose results in:

- death;
- is life threatening (at the time of the event);
- requires hospitalisation or prolongation of existing inpatients' hospitalisation;
- results in persistent or significant disability or incapacity;
- is a congenital anomaly or birth defect;
- is a new event of the trial likely to affect the safety of the subjects, such as an
- unexpected outcome of an adverse reaction, lack of efficacy of an investigational medicinal product used for the treatment of a life threatening disease, major safety finding from a newly completed animal study, etc.

All SAEs will be reported to the accredited METC that approved the protocol, according to the requirements of that METC.

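### Tinnitus relief is tested across patients with and without tinnitus, and the imputation rule makes no exception for tinnitus scores that do not apply

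*Protocol*

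**What the plan says.** Section 8 of the protocol gives the aim as clinical outcome after cochlear implantation, "measured as speech perception in noise, sound localization, tinnitus and quality of life in patients with SSD". Three instruments serve the tinnitus part (section 6.1.2): the Tinnitus Handicap Inventory (THI), the Tinnitus Questionnaire (TQ) and the Tinnitus Burden Questionnaire. Of the last, section 6.3.2 says: "This questionnaire contains 12 questions on the severity and character of tinnitus described by subjects".

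The inclusion and exclusion lists (sections 4.2 and 4.3) do not mention tinnitus. Section 5.1 lists the baseline forms without any condition: "Questionnaires: SSQ, HUI3, GBI, APHAB, TTO, VAS, EQ5D, HADS, and Tinnitus questionnaires". For follow-up in all groups, section 3 says "All questionnaires outlined in section 6.1.2. will be filled out".

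For continuous secondary outcomes, section 8 plans "Kruskal Wallis tests for continuous outcomes" between groups and paired t-tests within subjects. Neither is restricted or stratified by tinnitus at entry. The missing-data rule is one general sentence: "Missing values will be imputed using multiple imputation and all analyses will be performed on an intention-to-treat basis".

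Two other places set the direction of the expected effects. Section 1.2 argues that an implant relieves existing tinnitus by restoring afferent input. Section 7.2 names, among the adverse events specific to the implant, "complaints associated with electrical stimulation (i.e. tinnitus, facial nerve stimulation, dizziness").

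**The concern.** The rationale concerns patients who have tinnitus, whereas the planned comparison covers everyone. For a patient without tinnitus at entry, the forms can come back in one of two states, and neither serves the relief question.

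- **Completed at the floor.** The patient has no room to improve. Relief in sufferers is averaged with patients who cannot show any, and new tinnitus in implanted patients is subtracted from it. The paired t-tests are diluted in the same way.
- **Left blank.** The score does not apply, but the rule in section 8 does not distinguish that from a missing score. Imputation would then supply a value informed mainly by patients who do have tinnitus.

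At stake is a named aim: a real reduction of tinnitus could be missed, and relief and new onset could not be told apart in the questionnaire results.

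**Working it through.** **Figures in the plan.** The protocol gives no effect size, prevalence or power for tinnitus. Its only sample-size figure concerns the modified Plomp test (5 dB, SD 5 dB, alpha 0.05, power 95%). A two-sided t-test gives 26.99, so 27 per group, and 30 after the 10% margin. That reproduces section 4.4 and has no bearing on tinnitus.

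**Inputs.** From section 6.2: 30 patients in group A, 45 in B and 45 in C. Assumed, not in the protocol:
- share p with tinnitus at entry of 50, 70 or 90%;
- scores of sufferers with SD 1 and mean 2.0 in B and C and 1.2 in A (an effect of 0.8 SD), truncated at 0;
- patients without tinnitus score 0;
- no new tinnitus, unless stated.

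Section 8 names three groups for the primary outcome. I read the Kruskal-Wallis tests for secondary outcomes as using the same three randomised groups.

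**Step 1: how many patients are affected.** Patients without tinnitus = 120 × (1 − p) = 60, 36 or 12. Of these, 15, 9 or 3 are in group A and 45, 27 or 9 in B and C together. These are the largest numbers that could be imputed for this reason, reached only if all of them leave the forms blank.

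**Step 2: dilution if the forms are completed.** The all-patient mean difference is p times the difference in sufferers: 0.5 × 0.8 = 0.40, 0.7 × 0.8 = 0.56 and 0.9 × 0.8 = 0.72 SD before truncation.

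A two-sample mean comparison (30 v 90) gives a first look. The variance in a mixed group is p(1 + m²) − (pm)². At p = 0.5 this is 0.5 × 5 − 1 = 1.50 for m = 2.0 and 0.5 × 2.44 − 0.36 = 0.86 for m = 1.2. The average is 1.18, the SD 1.086, and the standardised effect 0.40 / 1.086 = 0.37. At p = 0.7 and 0.9 it is 0.50 and 0.67.

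The planned rank test does worse in the whole cohort, because a large block of patients is tied at the floor. Simulated power, with alpha 0.05:

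| Share with tinnitus | t-test, 30 v 90: all patients | t-test: sufferers only | Three-group Kruskal-Wallis: all patients | Three-group Kruskal-Wallis: sufferers only |
|---|---|---|---|---|
| 50% | 41% | 75% | about 15% | about 60% |
| 70% | 65% | 88% | about 39% | about 77% |
| 90% | 89% | 95% | about 76% | about 86% |

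The t-test columns come from the formula without truncation, and the Kruskal-Wallis columns from simulation with it. The subset is smaller (15, 21 or 27 in A; 45, 63 or 81 in B and C) but has the higher power in every row.

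**Step 3: netting against new tinnitus.** Put the same assumptions on a 0 to 100 scale (SD 20, means 40 and 24) and let 10% of tinnitus-free patients in A develop tinnitus with mean score 20. In a two-group Kruskal-Wallis comparison of 30 v 90, the all-patient difference falls from 7.5, 10.7 and 13.5 to 6.6, 9.8 and 13.4 points. Power falls from about 18, 51 and 86% to about 11, 41 and 85%. The difference in sufferers stays near 15 points.

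**Step 4: the other branch, blank forms.** If tinnitus-free patients score 0, the mean in B and C is p × 40 = 20, 28 or 36. If all their forms are blank and filled from sufferers, it becomes about 40 at every prevalence. No power is given for this branch, because the check used a single imputation draw rather than multiple imputation.

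**The case against.** A reader might infer that the plan as written invents tinnitus scores. The protocol does not support that. Section 3 says the questionnaires will be filled out, and if tinnitus-free patients return floor scores, nothing is imputed for this reason. Imputation needs a blank form that is then coded as missing. Nor do the two problems add up: for a given patient and visit, a form is either completed or blank. The items and scoring of the forms are not shown, and only the Burden Questionnaire is described as asking about severity and character, so floor scoring is itself an assumption.

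A reader might also infer that the all-patient comparison is invalid. It is not: it compares randomised groups on net tinnitus burden and respects intention to treat. Nor does new tinnitus go unrecorded. Section 7.2 records all adverse events that are reported or observed and names tinnitus among those specific to the implant. What is lost is the separation of relief from new onset in the questionnaire analysis.

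Finally, scoring rules and subsets are often left to a statistical analysis plan, which may exist, and tinnitus is one of many secondary outcomes with no power claim. All this limits the weight of the point. It does not remove it, because section 8 itself fixes a comparison with no separation by baseline tinnitus and an imputation rule with no exception, and both sit badly with the rationale in section 1.2.

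**Conclusion.** The point holds as a mismatch between a stated aim and the fixed analysis. The planned comparison answers whether net tinnitus burden differs between the groups. It is a weak test of whether an implant relieves existing tinnitus, and the general imputation rule leaves open that a score which does not exist is filled in from sufferers.

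The direction of the dilution follows from the design whenever some patients enter without tinnitus and score at the floor. Its size does not: it rests on an assumed prevalence, effect and score distribution. Over the assumed range it runs from severe at 50% prevalence to modest at 90%. The change is worth making, but the primary analysis does not depend on it.

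**What to change.** In section 8:

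1. Make the tinnitus-relief analysis of THI, TQ and Burden scores a comparison by randomised group in patients with tinnitus at baseline. Baseline status precedes treatment, so the comparison stays randomised. Keep the all-patient net-burden comparison as supportive.
2. In patients without tinnitus at baseline, report new tinnitus by randomised group, alongside adverse-event recording.
3. Do not impute tinnitus scores that do not apply; use multiple imputation only for values that are truly missing. Give a defined score to a baseline sufferer whose tinnitus has gone, so that complete relief is neither imputed away nor dropped.

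To support this, record presence of tinnitus (yes or no) at baseline, before the allocation is known, and at each visit.

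The cost is wording and one short item, since the questionnaires are already collected at baseline. The downside is fewer patients in the relief comparison: 60, 84 or 108 of 120 at 50, 70 or 90% prevalence.
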